## **18 Economic evaluation**

### **18.1 Design**

Two cost-effectiveness analyses (one for each trial) will be conducted using decision analytic modelling. Both analyses will be conducted from the perspective of the NHS. To help inform decision making around the future implementation of A&F, the analysis requires a direct comparison of the costs and effects of all four A&F options (conventional A&F, enhanced content only, post-feedback support only, and combined enhanced content and post-feedback support) so as to determine which is likely to be the most cost-effective alternative and offer the best value for money. These works will draw on a variety of data collected specifically during the trial (see section 13 above and section 18.2 below), together with data generated elsewhere within and beyond the AFFINITIE Programme.

### **18.2 Methods**

Trial-based economic evaluation is not feasible in this instance as no unique set of patients is identified at the start of the trial and followed until study completion. Health economic modelling is therefore required to simulate the costs and outcomes associated with the developed enhancements (separately and combined) as compared with current practice. Two models will be needed, one for patient blood management in surgery and one for haematology as the interventions will target these different transfusion topics and because the costs and adverse event profiles also differ between these components. The models will

be developed jointly by the CI and the project economist following a literature review of previously published models of transfusion, and in accordance with good practice guidelines for decision modelling. A number of transfusion specialists/haematologists external to the project will be asked to comment on the proposed model structure.

The models will combine decision tree and Markov approaches and will be structured so as to simulate the main hypothesised costs and effects. These include the costs associated with delivering standard and enhanced feedback interventions, the potential reduction in unnecessary transfusions and associated adverse events with their costs and consequences, as well as any change in clinical practice occurring to facilitate the reduction in transfusion e.g. for the surgery audit topic this might be better management of pre-surgery anaemia, use of tranexamic acid, or intra-operative cell salvage, all of which have associated costs which must be considered.

As detailed in section 13.6 above, data will be collected on a small sample of the clinical audit proformas used in the trials on time taken by hospital staff to identify and extract the required audit data during the trials. The time taken to enter these data onto the NCA on-line system will be estimated by members of the research team performing the data entry for a sample of 'mock' audit cases. These data will allow costs of the current NCA audit process to be quantified and will provide data for costing any new re-audits implemented at sites attempting to change behaviour following receipt of the post-feedback support). The resources required to design and populate the standard and enhanced versions of the feedback documents will be identified by asking the NCA clinical audit leads and statistician to record the amount of time required to perform such activities. Project team members delivering the 'post-feedback support' intervention will record the duration and attendance of personnel at the training session provided to each Hospital Transfusion Team. Data on whether hospitals then act upon the guidance given will be collected by a subsequent AFFINITIE work stream (work stream 3). The trials will also provide data on the current rate of unnecessary transfusions and the relative effectiveness of the interventions in reducing this rate for populating the model. Data will also be available via the trials on the volumes of blood components transfused to each audit case so as to estimate the mean number of product units per unnecessary transfusion. The organisational survey conducted at baseline and follow-up will include information on the components of patient blood management conducted at hospitals before and after the audit and will allow identification and costing of increased uptake of patient blood management policies in each trial arm. A combination of data from the published literature, expert clinical opinion, the UK haemovigilance system (Serious Hazards of Transfusion (SHOT)) and the Blood Stocks Management Scheme (BSMS), will be used to estimate the probability, cost, HRQoL, and survival impact of transfusion-related adverse events.

### **18.3 Analysis**

A lifetime horizon will be used for the analysis and model results for each intervention will be reported as mean discounted costs and a series of outcomes (for example adverse events, life years, and quality adjusted life years). Incremental analyses will compare the costs and effects of each of the interventions versus standard A&F. Structural uncertainty in the model will be examined using sensitivity analysis and the model's internal consistency assessed using extreme value sensitivity analysis. Parameters will be entered into the model as

distributions and probabilistic sensitivity analysis used to assess the impact on the cost-effectiveness results of joint parameter uncertainty.

Cost effectiveness acceptability curves will identify the intervention most likely to be cost-effective for different values of willingness to pay for additional health gain. We shall liaise with the National Comparative Audit Team, SHOT, and NHSBT to ascertain whether any independent data are available to facilitate the external validation of the model.

The general methodology utilised to perform the cost-effectiveness analysis of the A&F interventions here will be described within a health economic analysis plan and will feed into the bank of resources planned for the knowledge exchange phase of the programme.

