### **6.2 Secondary Objectives of the trials**

Secondary objectives are:

- To generate data to serve as inputs for an investigation of the relative cost-effectiveness of the two feedback interventions compared to usual NCA feedback in each audit topic from a NHS perspective
- To investigate whether the two feedback interventions reduce volume of blood products transfused (i) across specialities within NHS trusts and health boards and (ii) for patients treated in specialities targeted by transfusion topics, when compared to usual feedback, 12 months following randomisation
- To investigate whether two feedback interventions reduce the number of errors (defined in the Statistical Analysis Plan) reported to SHOT, when compared to usual feedback, 12 months following randomisation
- To explore whether there are differential predictors (or moderators) of the effects of the two feedback interventions when compared to usual feedback (i.e. subgroup effects)
- To explore the mechanisms by which the two feedback interventions affect outcome (i.e. mediators of the treatment effect)
- To explore whether the effect of the two enhanced feedback interventions when compared to usual feedback differs according to the transfusion topic

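### The incremental economic analysis in section 18.3 is set against standard A&F and does not deliver the four-way comparison that section 18.1 requires

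*Protocol*

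**What the plan says.** Protocol section 18.1 states that "the analysis requires a direct comparison of the costs and effects of all four A&F options", and lists them as "conventional A&F, enhanced content only, post-feedback support only, and combined enhanced content and post-feedback support". The purpose is given as "so as to determine which is likely to be the most cost-effective alternative and offer the best value for money".

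Section 18.3 then sets the incremental rule: "Incremental analyses will compare the costs and effects of each of the interventions versus standard A&F". The same comparator appears in section 18.2, where the models are to "simulate the costs and outcomes associated with the developed enhancements (separately and combined) as compared with current practice", and in section 6.2, where the objective is the "relative cost-effectiveness of the two feedback interventions compared to usual NCA feedback in each audit topic from a NHS perspective".

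Section 18.3 has two further outputs. Discounted mean costs and outcomes are reported for each intervention, and "Cost effectiveness acceptability curves will identify the intervention most likely to be cost-effective for different values of willingness to pay". The general methodology "will be described within a health economic analysis plan", which is not at hand.

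**The concern.** A trust can adopt only one of the four options, so the decision turns on what each step up in cost buys. For the combined package, the relevant step is from a single component to both. An increment measured from standard feedback averages over the two components. An effective component can therefore carry an ineffective one, and the package can pass a cost-effectiveness test that its second component would fail.

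What is at stake is the adoption message of the economic evaluation. The protocol itself gives reason to care about this step: section 7 records doubt that the two interventions would have additive effects, and section 16.2 plans for a small antagonistic interaction.

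**Working it through.** The protocol states no cost, QALY, incremental ratio or threshold, so there is no figure of its own to reproduce. The check sets the sections against each other and then illustrates the consequence.

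**1. Comparisons required and comparisons stated.** Four options give 4 × 3 / 2 = 6 pairwise comparisons. Section 18.3 states three, each against standard. The three not stated are combined v documents, combined v support, and documents v support. The first two show whether a second component is worth adding.

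**2. What the stated comparison contains.** Let C and E be mean cost and effect, with subscripts 0 (standard), D (documents), S (support) and DS (both).

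- Package against standard: (C_DS − C_0) / (E_DS − E_0)
- Adding support to documents: (C_DS − C_D) / (E_DS − E_D)

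The first ratio contains neither C_D nor E_D, so on its own it cannot answer the second question.

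**3. At the protocol's planning values.** Section 16.2 gives 20% unnecessary transfusions with standard feedback, 14% with one component and at most 10% with both. Taking 10%, the first component removes 20 − 14 = 6 points and the second 14 − 10 = 4 points. Assume that each component costs k.

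- First component v standard: k/6 = 0.167k per point
- Package v standard: 2k/10 = 0.20k per point
- Second component v first: k/4 = 0.25k per point

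The second component costs 0.25/0.20 = 1.25 times as much per point as the ratio against standard suggests. This needs no assumption that a component is useless.

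**4. The extreme case: support has no effect.** All inputs are assumed: documents cost 1,000 and gain 0.20 QALY, support costs c and gains 0, and the threshold is 20,000 per QALY. The package's ratio against standard is (1000 + c)/0.20, which reaches the threshold at c = 20,000 × 0.20 − 1,000 = 3,000. Net benefit is 20,000 × 0.20 − 1,000 = 3,000 for documents and 3,000 − c for the package, so documents alone dominate at every positive c.

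The probabilities below come from 200,000 draws with independent normal effects (SD 0.08 QALY each), additive effects and fixed costs.

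| c | Ratio, package v standard | P(package beats standard) | P(package best of four) | P(documents best of four) |
|---|---|---|---|---|
| 500 | 7,500 | 0.865 | 0.365 | 0.605 |
| 1,000 | 10,000 | 0.812 | 0.257 | 0.713 |
| 2,000 | 15,000 | 0.671 | 0.103 | 0.868 |
| 2,900 | 19,500 | 0.519 | 0.034 | 0.935 |
| 3,500 | 22,500 | 0.414 | 0.014 | 0.956 |

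In the first four rows the package passes against standard although support buys nothing. In all five, a sequential comparison would exclude it, and acceptability curves drawn jointly over the four options would favour documents alone.

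**The case against.** A reader might infer that the whole economic analysis is confined to comparisons with standard feedback. The protocol does not support that. Section 18.1 calls for the four-way comparison, and section 18.3 reports results by intervention and plans acceptability curves to choose among interventions. As the last two columns of the table show, curves drawn over all four options would point away from the dominated package.

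A reader might also infer that the single-component arms play no part in judging the package. That is not established either. Section 18.2 feeds the interventions' relative effectiveness into the model, and section 16.3.4 estimates effects from one factorial model that uses all arms. Each single component is also compared with standard, so the missing contrast can be recovered by subtraction: NB_DS − NB_D = (NB_DS − NB_0) − (NB_D − NB_0). On the net-benefit scale, a common baseline ranks the options correctly.

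Nor are the high probabilities of the package beating standard false results. In the first four rows its net benefit against standard is truly positive. The error arises only if that verdict is taken as a reason to adopt the package over documents alone, and the protocol states no such adoption rule. Finally, rules on dominance would ordinarily sit in the health economic analysis plan.

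These points narrow the concern but do not remove it. Section 18.3 does not merely leave the comparator open. It names one that differs from the aim in section 18.1, and the later plan would inherit it. The section does not say that the curves are calculated jointly over all four options, and its incremental sentence uses the word interventions for options other than standard. A curve also gives the probability of being best. It does not give the incremental cost-effectiveness of adding a component, and the option most often best need not have the highest expected net benefit.

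**Conclusion.** The point holds as an inconsistency between adjacent sections: the stated incremental analysis does not deliver the four-way comparison that section 18.1 says is needed. Read alone, the package's increment against standard can make it look good value when its second component adds cost and little or no benefit. The other planned outputs would expose this in part.

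The size cannot be fixed from the protocol. The 1.25-fold understatement rests on the planning proportions and equal component costs. The zero-benefit scenario rests wholly on assumed costs, QALYs, SDs and threshold. Both show the mechanism and do not forecast results. The matter concerns a secondary, model-based analysis; the primary effectiveness analyses and the data collection are unaffected.

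**What to change.** In section 18.3, replace the incremental sentence with a fully incremental analysis across the four options. Order them by mean cost, remove dominated and extendedly dominated options, and compare each remaining option with the next less costly non-dominated one. State that expected net benefit and the acceptability curves are calculated jointly over all four options, standard included. Keep the comparisons with standard as supplementary, which still serves sections 6.2 and 18.2, and carry the same wording into the health economic analysis plan.

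The change uses the same model output and needs no new data. It costs a small amount of extra reporting, and one or more enhanced options may be shown as dominated, which is less favourable than a ratio against standard.

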## **19 Clinical governance issues**

Audit and feedback is a widely used quality improvement method which seeks to improve patient care and outcomes through careful review of health care performance against explicit standards. The aim of this trial is to evaluate different enhanced feedback interventions, targeted at individuals, teams, or services, to improve the impact on patient care. Therefore, the interests of the patients will be guarded by the normal duties of care.

Members of the NCA will feedback any issues to the individual NHS Organisations in line with appropriate information and clinical research governance requirements, as per usual practice in national audits.

Members of the central trial team who are involved in the delivering of the intervention will have the opportunity to highlight any issues of concern with the Trial Management Group, the Trial Steering Committee and to individual NHS Organisations in line with appropriate information and clinical research governance approval procedures.

## **20 Quality assurance & ethical considerations**

### **20.1 Quality assurance**

The study will be conducted in accordance with the principles of Good Clinical Practice (GCP) in clinical trials, as applicable under UK regulations, the NHS Research Governance Framework (RGF) and through adherence to CTRU Standard Operating Procedures (SOPs).

### **20.2 Serious breaches**

Investigators are required promptly to notify the CTRU of a serious breach (as defined in the latest version of the National Research Ethics Service (NRES) SOP).

A 'serious breach' is defined as a breach of the protocol or of the conditions or principles of GCP (or equivalent standards for conduct of non-Clinical Trial of Investigational Medicinal Products (CTIMPs) which is likely to affect to a significant degree the safety or physical or mental integrity of the trial subjects, or the scientific value of the research.

Any unintentional disclosure of named patient or professional will be reported to NCA and the Trial Steering Committee and site concerned and will be handled in accordance with relevant Guidance.

In the event of doubt or for further information, the Investigator should contact the Trial Co-ordinator at the CTRU.

### **20.3 Ethical considerations**

AFFINITIE will use an existing, established NCA as a platform to evaluate feedback interventions. The NHS BT NCA has previously performed national audits in approximately 98% of English Trusts, the majority of the Health Boards in Wales, ~50% of the Health Boards in Scotland and 100% of the Health and Social Care Trusts in Northern Ireland.

The NCA operates within robust information governance arrangements which are provided to the site at recruitment. Requirements for clinical audit are outside the remit of this trial protocol and will be followed in line with local practice for Clinical Audit oversight.

In line with the NCA standard practice, local hospitals will hold “linkage records” for patients and health professionals to facilitate the clinical audit data collection. The data entered online to the trial database will be unlinked and anonymised, and we will therefore not require individual consent from patients or health professionals. The NCA will ensure that robust processes are in place for the transfer of clinical audit data in line with best practice.

Ethical approval is not sought for the conduct of the clinical audit (with regards to design, data collection or analysis) of the audit as these are covered by local governance requirements. The interests of patients will be guarded by the normal duties of care. We will follow appropriate information and clinical research governance approval procedures.

The targets of the interventions are NHS professionals who are routinely involved in cascade of the feedback following a clinical audit; specifically:

- Hospital Transfusion Teams, Hospital Transfusion Committees
- Audit Departments and laboratories
- Senior clinicians / junior doctors
- Matrons / nurses
- Governance and Divisional Managers

The study will be submitted to and approved by a main Research Ethics Committee (REC) and will receive management approval for each participating NHS Trust/ prior to randomisation. The CTRU will provide the Main REC with a copy of the final protocol and all other relevant study documentation.

As this is a cluster trial, consent for participation in the trial will be obtained at the organisational level (i.e. by the NHS Trust / Health Board). Individual consent from the NHS Professionals in receipt of the feedback will not be obtained.

We will discuss any identified potential serious concerns about clinical practice with the NCA, Trial Steering Committee and relevant Trust or Health Board.

## 21 Confidentiality

Local clinical audit data will be stored and retained securely in accordance with the host organisations procedures.

All paper and electronic information collected by the NCA and the CTRU during the course of the project will be kept strictly confidential and will be retained and stored securely.

The project will comply with all aspects of the Data Protection Act 1998 and operationally this will include:

- Ensuring clinical audit data received by the NCA is anonymised and that only the instructed identifiers are present before sending to CTRU.
- Ensuring all data transferred to the CTRU is stored, handled and processed in accordance with the principles of the 1998 Data Protection Act, the operation of a Data Transfer Agreement, study specific guidance and the Study Publication Policy

## 22 Archiving

In accordance with the Department of Health's *Records Management NHS Code of Practice*, clinical audit records must be retained for securely for a minimum of 5 years after the clinical audit has completed. Arrangements for confidential destruction will be in line with the host organisation.

In accordance with the Sponsors policy, data collected for the purposes of the AFFINITIE trial evaluation will be securely archived for a minimum of 5 years after completion of the trial. Arrangements for confidential destruction will then be made.

No records may be destroyed without first obtaining written permission from the Sponsor.

## 23 Statement of indemnity

This study is sponsored by the NHS Blood and Transplant (NHS BT) and the NHS indemnity scheme will apply to meet the potential legal liability of the sponsor for negligent harm caused harm to participants arising from the management of the research.

Participants are NHS staff and indemnity to meet the potential legal liability of investigators/collaborators arising from harm to participants in the conduct of the research will be provided through the NHS schemes or through professional indemnity.

## 24 Study Organisational Structure

The general responsibilities are outlined below:

### 24.1 Sponsor

The Sponsor (NHSBT) is the organisation that takes responsibility for arrangements to initiate, manage, monitor and finance the trial. The Chief Investigator is employed by the NHSBT.

## **24.2 Chief Investigator**

As defined by the NHS RGF, the Chief Investigator is responsible for the design, management and reporting of this study, the whole research programme and its constituent parts.

This trial will use an existing national audit platform, the National Comparative Audit, to evaluate audit and different types of feedback with the aim to reduce unnecessary transfusions. The background of the trial is standard practice and any intervention above standard practice will be delivered by a central trial team. The Chief Investigator will be accountable for the delivery of the feedback (intervention) and a Principal Investigator at each participating NHS Trust is not required. The supporting rationale for this is as follows:

- The target of the intervention are the staff employed by the NHS Trust. The role of a local Principal Investigator in this trial could draw additional attention to the trial and hence act as an unintended influence on local transfusion practice, thereby diluting any observed effect size of the interventions. It will not be possible to quantify the effect of this role which could undermine the scientific integrity of the trial.
- The intervention under investigation will be delivered by Intervention Providers who are part of a central team. The enactment following receipt of the intervention is part of the evaluation research and needs to follow real life as far as possible.

